#### Feasibility and retention strategies

To reduce fatigue and attrition, the intervention is delivered sequentially, with each level standardized to a two-month period. Telephone delivery of the individual- and interpersonal-level components aim to minimize mobility and scheduling barriers, with sessions arranged according to participants’ availability, with reminder calls provided by the research team. Based on prior experience (58), missed sessions are expected to be minimal. In the event if happens, sessions will be rescheduled within the intervention period and attendance will be documented. The community-level component is limited to four socially engaging, event-based sessions to reduce burden while promoting connection.

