### Planned statistical analysis

Descriptive statistics will be used to summarize baseline characteristics of the participants within each arm. An intention-to-treat approach will be adopted. Missing values will not be replaced because mixed-effects models can accommodate participants with at least one outcome measurement under the assumption that data are missing at random. All analyses will be appropriately accounted for the cluster randomized controlled trial (cRCT) design, recognizing that participants are nested within clusters and outcomes within clusters may be correlated. To assess intervention effects of different arms on primary and secondary outcomes, generalized linear mixed models (GLMM) with random intercepts for clusters, fixed effects for time points (i.e., T0, T1, T2, T3, T4, T5), group (using the control group as the reference), and their interaction terms will be utilized. In addition to GLMM, generalized estimating equations (GEE) with robust standard errors and an exchangeable working correlation structure will be used for sensitivity analysis, with small sample corrections applied as needed to control the rate of type I error. To ensure robustness, results from GLMM and GEE approaches will be compared, with multiple testing corrections such as Bonferroni adjustments applied as appropriate. Sensitivity analyses will include per-protocol and complete case approaches to evaluate the influence of adherence and missing data. Mediation analyses of psychosocial and other potential mediators will employ multilevel modelling techniques suited for clustered data. Statistical significance was defined as *p* < 0.05. All statistical modelling will be conducted using SPSS version 29.0, which provides robust tools for multilevel mixed-effects modelling including GLMM and GEE, with options for controlling cluster effects and covariate adjustment.

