Despite these strengths, the study presents several potential challenges. First, participants in the more intensive arms (i.e., individual- + interpersonal-level; and individual- + interpersonal- + community-level) may experience adherence difficulties or intervention fatigue. To mitigate these issues, flexible scheduling will be offered to accommodate participants’ energy levels, health conditions, and personal circumstances. Intervention intensity will also be adjusted to individual needs without compromising the core therapeutic components. For example, volunteers may devote additional time to selected topics, provide tailored feedback or supplementary materials in coordination with the project team, and employ a variety of engagement techniques to support diverse learning styles. A second limitation concerns the risk of participant attrition, particularly given the extended 24-month follow-up period. To address this, monthly check-ins and milestone-based financial incentives will be provided after the intervention period to encourage continued participation, maintain rapport, and reduce dropout rates.

Overall, this study is expected to generate rigorous evidence regarding the effectiveness of multilevel interventions to reduce loneliness among older adults, especially those living with poverty and intersecting social vulnerabilities. By integrating individual, interpersonal, and community components—and leveraging social capital through trained volunteers and technology-supported communication—the intervention is designed to be effective, accessible, affordable, and scalable. The longitudinal design enables the examination of both short- and long-term outcomes, offering insights into sustainable best practices. The findings are anticipated to guide policymakers, practitioners, and community organizations in developing programmes that strengthen social connectedness, improve quality of life, and promote healthy aging at a population level.

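### Complete case and per-protocol are weak choices for the jobs the plan gives them: one does not examine outcomes missing not at random, the other is not a randomised comparison

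*Protocol article*

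**What the plan says.** All of this is in the Protocol article, Planned statistical analysis, unless noted.

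- Missing values are not imputed. The mixed model is relied on "under the assumption that data are missing at random".
- The primary model is described as "generalized linear mixed models (GLMM) with random intercepts for clusters", with fixed effects for visit, group and their interaction.
- GEE has its own role: "To ensure robustness, results from GLMM and GEE approaches will be compared". Robust standard errors and small-sample corrections go with it.
- Adherence and missing data have separate checks: "Sensitivity analyses will include per-protocol and complete case approaches to evaluate the influence of adherence and missing data".
- The Sample size estimation section allows for 15% attrition across 24 months.
- On adherence, the Discussion says that participants in the two more intensive arms "may experience adherence difficulties or intervention fatigue". Feasibility and retention strategies expects few missed sessions and says that "sessions will be rescheduled within the intervention period and attendance will be documented".

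**The concern.** A sensitivity analysis for missing data is useful when it relaxes the assumption on which the primary analysis leans. The primary assumption here is MAR. The untestable worry is that people who leave are lonelier, or less lonely, than their observed history predicts, and that this differs by arm. Complete case moves the other way: in general it is valid when missingness is completely random or depends only on covariates in the model. If it agrees with the mixed model, the MNAR question remains open. If it disagrees, the cause may be its own bias.

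Per-protocol has a different fault. It compares people chosen by what they did after allocation, and the arms ask very different things of them. A difference among adherers mixes the effect of the intervention with the traits of those who keep attending.

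The stake is false reassurance. Objectives 2 and 3 are incremental comparisons between arms of unequal burden, so an arm-specific departure would bear directly on them.

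**Working it through.** **Plan's own figures.** 4 x 336 = 1,344. Attrition of 15% gives 0.15 x 1,344 = 201.6, about 202 people missing by 24 months. The article gives no figure for the size of a departure from MAR. The sample size itself cannot be reproduced, because no SD is stated.

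**1. Shift from a departure confined to one arm.** Let p be the share missing in the arm, and δ the amount by which the missing outcomes differ from what MAR predicts. Then shift in the arm mean = p x δ. Take p = 0.15 (the planned overall rate, assumed to hold in that arm) and δ = 0.2 to 0.5 SD (assumption):

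- 0.15 x 0.2 = 0.03 SD
- 0.15 x 0.5 = 0.075 SD

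**2. Scale against the planned effect.** The target of 0.087 units has no SD, so the standardised effect has to be back-solved. With 32 estates over four arms:

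- Retained per arm: 336 x 0.85 = 285.6; per estate: 285.6 / 8 = 35.7
- Design effect: 1 + 34.7 x 0.028 = 1.97
- Effective n per arm: 285.6 / 1.97 = about 145
- Implied standardised effect at two-sided 5% and 95% power: (1.960 + 1.645) x √(2/145) = about 0.42

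On that reading the shift is 0.03/0.42 = 7% to 0.075/0.42 = 18% of the planned effect.

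**3. Per-protocol.** Contact time from Table 2 and the Structure section:

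- Arm 1: 8 x 60 + 16 x 15 = 720 min
- Arm 2: 8 x 60 + 8 x 60 + 8 x 15 = 1,080 min
- Arm 3: 8 x 60 + 8 x 60 + 4 x 120 = 1,440 min
- Control: six monthly messages, no sessions to miss

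If exclusions fall in the active arm only, confounding bias = share excluded x prognostic gap between retained and excluded participants. For 10-30% excluded and a gap of 0.2-0.8 SD (both assumptions), this runs from 0.10 x 0.2 = 0.02 SD to 0.30 x 0.8 = 0.24 SD.

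**4. Does comparing the planned analyses reveal MNAR?** This was checked by a large-sample simulation: 250 estates of 42 per arm, two arms, six visits, ICC 0.028, within-person correlation 0.6 (assumed). The true change effect at the last visit was set at -0.30 SD. In the MAR and MNAR settings, dropout was unrelated to outcome in control. In the active arm it rose with loneliness, through the last observed value for MAR and the current value for MNAR. Monte Carlo SE was 0.005-0.007.

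| Analysis | MCAR | MAR | MNAR |
|---|---|---|---|
| Mixed model, estate intercept only (as named) | -0.31 | -0.38 | -0.38 |
| Mixed model, estate and participant intercepts | -0.31 | -0.30 | -0.33 |
| GEE, exchangeable within estate | -0.31 | -0.38 | -0.38 |
| GEE, exchangeable within participant | -0.31 | -0.30 | -0.33 |
| Complete case | -0.31 | -0.29 | -0.31 |

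To three decimals, the model with participant intercepts and complete case differ by 0.302 - 0.288 = 0.014 under MAR and 0.327 - 0.309 = 0.018 under MNAR. The gap is much the same whichever mechanism is true, so it does not separate them. Only direction and ranking should be read from this table, because the mechanisms are assumed.

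**The case against.** Several stronger readings are tempting, and the documents do not support them.

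- **A reader might infer that every planned sensitivity analysis, GEE included, assumes more than the primary model.** The article uses GEE as a robustness check on the model. With robust standard errors it relaxes the distributional and covariance assumptions. Unweighted GEE does not probe MNAR either, but it does not rank below the primary model as named. In the table, estate-level GEE equals the estate-intercept mixed model, and participant-level GEE does better under MAR. A mixed model with only an estate intercept ignores within-person correlation and does not itself earn MAR validity.
- **A reader might infer that the plan claims to test MAR, or to give an unconfounded adherence effect.** It claims neither. No analysis of observed data can test MAR, and that applies equally to a tipping-point analysis. What can be asked is that departures be examined.
- **A reader might infer that complete case must be badly biased or blind to trouble.** In the simulation it lay close to the truth and differed from the estate-intercept model. That depends on the assumed mechanism and does not turn it into an MNAR analysis.
- **A reader might infer that the protocol expects dropout to differ by arm.** The Discussion speaks of possible adherence problems in the intensive arms but ties attrition to the length of follow-up, with mitigation for both. Arm-differential dropout is therefore an inference.
- **The list of sensitivity analyses is not worded as exhaustive.** Delta-adjusted or complier-average analyses may stand in a statistical analysis plan that is not shown, so their absence alone is no finding.

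What remains is a criticism of what the article does fix: the method named for each of two stated purposes.

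**Conclusion.** The point holds in this narrow form. Complete case is a poor instrument for judging the influence of missing data when the primary analysis already rests on MAR. Per-protocol is a poor one for judging adherence when control has no sessions to miss. None of the named analyses examines departures from MAR.

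The missing-data shift is modest, 0.03 to 0.075 SD in one arm's 24-month mean. It assumes 15% missing in that arm and a departure of 0.2 to 0.5 SD. The 15% covers 24 months and should not be carried to the 2- to 6-month visits. The per-protocol range of 0.02 to 0.24 SD rests wholly on assumed exclusions and prognostic gaps, and on adherence being defined by sessions. The conventional intention-to-treat analysis is not undermined. This is a cheap improvement.

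**What to change.** 1. Keep GEE as a check on the model and describe it as that only.
2. Add to complete case, or use in its place, a delta-adjusted multiple-imputation analysis. The imputation model should respect both estate and participant clustering. Vary the shift by arm, including shifts in one arm alone, until the conclusion changes, and report that tipping point.
3. Label the per-protocol result as descriptive.
4. Optionally, supplement it with a complier-average effect for each active arm against control, using allocation as the instrument and the attendance already being recorded. State the exclusion restriction openly. It is doubtful where partial attendance can itself help, so this is a supplement and not an automatic replacement.

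The cost is extra analysis work, possibly in software other than the SPSS version named in the plan. No new data are needed. The change should be fixed before outcomes are seen.

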At the community level, social infrastructure and neighbourhood cohesion play a central role in mitigating loneliness. Access to local social resources and supportive neighbourhood environments protects individuals at risk of loneliness (40, 41). Evidence suggests that interactions with neighbours may confer greater benefits for mental, cognitive, and physical health—lower mortality risk—than family engagement alone (23). In Hong Kong, neighbourhood collective efficacy has been identified as a protective factor that buffers the adverse effects of poverty on loneliness (3). Community-based, event-driven community interventions have also demonstrated effective in improving older adults’ mental well-being by strengthening neighbourhood connections and fostering social cohesive environment (42). Since its launch in 2003, the Neighbours Every Day (NED) programme in Australia has successfully promoted neighborly engagement through locally organized events, leading to sustained improvements in neighbourhood affinity, social cohesion, and reductions in loneliness (43). These benefits persisted for at least 6 months, with participants reporting stronger neighbourhood ties and larger social networks than non-participants (44, 45). Thus, our community-level intervention will implement in-person, community-led events modeled after the Neighbours Every Day programme.

Notably, there is a lack of longitudinal data on the sustained effects of loneliness interventions on health, cognition, and healthcare utilization (46). To address this gap, the present study will conduct follow-up assessments over 2 years to compare the effectiveness of the individual only, individual + interpersonal, and individual + interpersonal + community interventions against an education-only control group (Figure 1). In addition, we will examine the mechanisms through which these interventions exert their effects and assess their cost-effectiveness to inform resource allocation. This study will clarify not only the comparative effectiveness of each intervention level but also the underlying mechanisms and cost-effectiveness, providing essential evidence for the scalable implementation of community-based programmes.

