### Objectives

This primary objective of this study is to develop, implement, and evaluate a multi-level intervention comprising individual-, interpersonal-, and community-level components to reduce loneliness and enhance well-being among older adults in Hong Kong. The specific goals are to:

Evaluate the short-term effectiveness of the individual-level intervention, compared with an education-only control group in reducing loneliness.Assess the incremental benefit of adding an interpersonal-level intervention to the individual-level intervention in further reducing loneliness, compared with the individual-level intervention alone.Assess the incremental benefit of adding a community-level intervention to the combined individual- and interpersonal-level intervention in reducing loneliness.Examine potential mediators through which individual-, interpersonal-, and community-level interventions influence loneliness outcomes.Examine the long-term effects of the individual-level only, individual- + interpersonal-level; and individual- + interpersonal- + community-level interventions, compared with an education-only control group, on loneliness, physical and mental health, cognitive functioning, and healthcare utilization.Evaluate the cost-effectiveness of individual-level only, individual- + interpersonal-level; and individual- + interpersonal- + community-level interventions compared with education-only control group.

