For the focus group discussions, all recordings will be transcribed verbatim by a research assistant. Two independent researchers will then conduct a thematic analysis of the transcripts using NVivo version 15 (95). The research team will review and agree on the identified codes, organizing them into main categories and subcategories. These categories may be condensed and reorganized as needed. The team will ensure consistency, reach consensus on the meaning and structure of the categories, and develop a finalized list. Ultimately, a set of categorized themes with supporting verbatim quotes will be produced to highlight the major strengths and limitations of the interventions and to inform improvements for their future implementation.

To evaluate the cost-effectiveness of the multi-level intervention compared to the control group, a trial-based economic evaluation will be conducted. Health outcomes will be measured as quality-adjusted life years (QALYs), calculated using the standard area-under-the-curve method based on individual EQ-5D-5L responses over the study period. Resource utilization will be estimated from the provider’s perspective, and costs for the intervention, outpatient care, emergency department visits, and inpatient care will be calculated using a bottom-up costing approach. The multi-level intervention will be considered dominant if it achieves higher QALYs at a lower cost than the control group. If it results in higher QALYs but also higher costs, the incremental cost-effectiveness ratio (ICER), defined as the difference in cost divided by the difference in QALYs (ΔCost/ΔQALYs), will be calculated. The intervention will be deemed cost-effective if it is dominant or if the ICER falls below the accepted willingness-to-pay threshold. The probability of the intervention to be accepted as cost-effective will be evaluated by probabilistic sensitivity analysis over the uncertainties of all parameters of costs and QALYs as well as variation of willingness-to-pay threshold from zero to 3× gross domestic product per capita in Hong Kong, presented as acceptability curves.

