## Discussion

Loneliness has increasingly been recognized as a major public health concern before, during, and after the COVID-19 pandemic. Although most existing interventions have focused primarily on the individual-level strategies, there remains a pressing need for more comprehensive, multilevel approaches capable of addressing the complex and interconnected determinants of loneliness. Building on our prior individual-level work (29, 30, 56, 58), the present study introduces a novel three-tier intervention for community-dwelling older adults experiencing loneliness and poverty (96). The primary aim is to develop, implement, and evaluate the effectiveness of three intervention intensities (i.e., individual-level only; individual- + interpersonal-level; and individual- + interpersonal- + community-level) on loneliness, assessed with the UCLA-LS and DJGL scales at 2-, 4-, 6-, 12-, and 24-month follow-ups, and to determine the most effective and sustainable configuration. A broad set of secondary outcomes—including physical and mental health indicators, cognitive functioning, and cost-effectiveness—will also be assessed over 24 months to capture the multidimensional impact and economic feasibility of these approaches.

A major strength of this study is its multidisciplinary team, bringing together expertise in intervention development, contextual understanding, and the design and execution of large RCTs. The involvement of key community partners (Oxfam Hong Kong, the Society for Community Organization, and the Research Centre for Gerontology and Family Studies) is essential for successful implementation. These organizations enhance access to individuals living in poverty, help engage other social service providers, and support the rapid resolution of challenges encountered during implementation. Another important strength is the use of telephone-based delivery and trained volunteers. This strategy leverages existing community resources, enhances scalability, and provides a cost-effective method for reaching older adults who may face mobility, financial, or digital barriers. Evidence from previous studies (29, 30) demonstrates that such approaches can enhance both operational sustainability and participant engagement (96).

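### Cost-effectiveness is judged only against the education control, so all three nested arms can pass and the rule cannot show whether an added level is worth its cost

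*Protocol article*

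**What the plan says.** The Objectives section sets the economic aim: "Evaluate the cost-effectiveness of individual-level only, individual- + interpersonal-level; and individual- + interpersonal- + community-level interventions compared with education-only control group". Planned statistical analysis follows it: "To evaluate the cost-effectiveness of the multi-level intervention compared to the control group, a trial-based economic evaluation will be conducted". Dominance is defined against the same comparator: "The multi-level intervention will be considered dominant if it achieves higher QALYs at a lower cost than the control group". The decision rule is: "The intervention will be deemed cost-effective if it is dominant or if the ICER falls below the accepted willingness-to-pay threshold". The ICER in that rule is the one introduced just before it, for an intervention with more QALYs and more cost than control. The acceptability curves are described for one intervention, as the probability that it is cost-effective. No comparison between active arms is planned for costs or QALYs.

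The Introduction gives the purpose: the trial will "assess their cost-effectiveness to inform resource allocation". It also motivates the trial by the shortage of sound evidence on the incremental benefit and cost-effectiveness of multi-level programmes. Objectives 2 and 3 are step-by-step comparisons (arm 2 with arm 1, arm 3 with arm 2), but for loneliness only.

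On missing data, the same analysis section says: "Missing values will not be replaced because mixed-effects models can accommodate participants with at least one outcome measurement". QALYs are to be "calculated using the standard area-under-the-curve method based on individual EQ-5D-5L responses over the study period". Table 1 schedules the quality-of-life measure at all six visits, T0 to T5.

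**The concern.** A funder can buy only one of the four options for a given estate. When options are mutually exclusive and each contains the one before it, the ICER of a larger package against control averages the value of its parts. A good return on the individual level can carry a weak interpersonal or community level past the threshold. The rule would then report that all three arms are cost-effective, which is true against control but does not say which to fund. It would also not flag an active arm that costs more and yields less than another active arm. The risk is that the largest package is adopted because it passed, when a smaller one gives more health for the same budget.

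A lesser concern is the missing-data rule. It is written without limit, but its only justification is a property of mixed models, and a QALY formed person by person is not a mixed-model outcome.

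**Working it through.** **No stated figure to reproduce.** The economic section gives no costs, QALY gains or threshold value (only a range up to three times GDP per capita). The check is therefore on the logic. All cost, QALY and threshold values below are assumptions.

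**Why the control ICER can hide a poor step.** Let arm 1 have cost c1 and QALY gain q1 over control, and arm 2 have c2 and q2. Then

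ICER(2 vs control) = c2/q2 = (q1/q2) × ICER(1 vs control) + ((q2 − q1)/q2) × ICER(2 vs 1).

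It is a weighted average. If most of the QALY gain comes from the first level, the step gets little weight.

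**Set A (assumed).** Threshold 400,000. Costs over control are 2,000, 4,000 and 6,500; QALY gains are 0.020, 0.022 and 0.024.

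| Arm | ICER vs control | ICER vs previous arm | Net benefit = 400,000 × QALY − cost |
|---|---|---|---|
| 1 | 2,000/0.020 = 100,000 | 100,000 | 8,000 − 2,000 = 6,000 |
| 2 | 4,000/0.022 = 181,818 | 2,000/0.002 = 1,000,000 | 8,800 − 4,000 = 4,800 |
| 3 | 6,500/0.024 = 270,833 | 2,500/0.002 = 1,250,000 | 9,600 − 6,500 = 3,100 |

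All three pass the stated rule. Both added levels fail, at 2.5 and about 3.1 times the threshold, and net benefit falls at each step.

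**Set B (assumed).** Costs are 3,000, 6,000 and 9,000; gains are 0.030, 0.036 and 0.040. ICERs against control are 100,000, 166,667 and 225,000. Step ICERs are 3,000/0.006 = 500,000 and 3,000/0.004 = 750,000. For thresholds between 225,000 and 500,000, all three arms pass but only arm 1 is efficient.

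**Set C: cost of arm 2 scaled to telephone time.** From Table 2 and the Structure section, telephone minutes per participant are:

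- Arm 1: 8 × 60 + 16 × 15 = 720
- Arm 2: 16 × 60 + 8 × 15 = 1,080
- Arm 3: 16 × 60 = 960, plus four 2-hour group sessions

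If arm 1 costs 3,000 and cost follows telephone time, arm 2 costs 3,000 × 1,080/720 = 4,500. With the gains of set B, its ICER against control is 4,500/0.036 = 125,000 and its step ICER is 1,500/0.006 = 250,000. The rule misleads between 125,000 and 250,000. Above 250,000 the added level is worth buying. So the size of the problem, and whether it arises at all, depends on the data.

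**Dominance between active arms.** Arm 3 has 1,080 − 960 = 120 fewer telephone minutes than arm 2. If the shared group sessions cost less per participant than those 120 minutes, arm 3 is cheaper than arm 2. If it also yields more QALYs, arm 2 is dominated, yet it could still pass against control. Unit costs are not given, so the cost order of the arms cannot be taken from their nesting.

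**Missing data (conditional).** T3 is at 6 months, and T4 and T5 are 12 and 24 months after completion, so the horizon is 6 + 24 = 30 months. Without T5 the last 12 of 30 months (40%) have no observed end point. Taking the planned 15% attrition as loss by T5, 0.15 × 1,344 ≈ 202 participants would have no full-horizon QALY and 0.85 × 1,344 ≈ 1,142 would.

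**The case against.** The strongest reply is that method and objective agree. Objective 6 asks for comparisons with control and the analysis delivers them. The incremental objectives concern loneliness, and the Discussion's aim "to determine the most effective and sustainable configuration" is also tied there to the loneliness scales. This stands: there is no internal contradiction, and that sentence is not evidence of an economic aim. It does not remove the problem, because the stated purpose is to guide resource allocation and the fixed decision rule cannot do that for nested options.

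A second reply is that arm-to-arm differences follow by subtraction from three comparisons with a common control. That is right for point estimates. It does not give their uncertainty, because the shared control makes the three comparisons correlated, and the decision rule does not use the differences anyway.

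A third reply is that the illustrative figures are invented. They are, and set C shows that other assumptions shrink the effect. A reader might also infer that the individual level is the cheap layer that carries an expensive package. The documents do not support this: by telephone time it is the largest single step, at 720 minutes against a further 360 for arm 2.

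On missing data, a reader might infer that anyone who misses one EQ-5D visit is dropped, and compound per-visit losses into a low complete share. The article does not say so. A missed visit between two observed ones can be bridged by the trapezoid rule, and complete case is named only as a sensitivity analysis. Detailed handling of missing economic data is also commonly left to a full plan that is not shown.

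**Conclusion.** The comparator point holds on the text alone: education-only control is the only economic comparator, and the rule can declare three mutually exclusive arms cost-effective together without showing whether either added level earns its cost. The size is unknown before data. Under the assumed sets, the step ICER for arm 2 runs from 250,000 to 1,000,000 while its ICER against control stays between 125,000 and 181,818. The point affects the resource conclusion, not the loneliness analysis.

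The missing-data point is secondary and conditional. The reason given for not replacing values does not cover a per-person QALY. If the rule were applied literally to QALYs, up to about 15% of participants would lack a full-horizon value. The documents do not state that they are excluded, and they give no figure on whether such loss is informative, so no bias can be claimed.

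**What to change.** Keep the three comparisons with control, and base the economic decision on a full incremental analysis:

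- Order the four arms by observed mean cost, not by their nesting.
- Remove dominated and extended-dominated arms.
- Report ICERs, or net benefit, between successive remaining arms.
- Present multi-arm acceptability curves that give, at each threshold, the probability that each arm is the optimal choice.

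Reword the economic paragraph so that it refers to the three active arms rather than to one intervention.

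Limit the no-replacement statement to the outcomes analysed by mixed models, and leave the handling of incomplete costs and QALYs to be set out with the economic analysis.

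The cost is analysis work only, with no new data. The drawback is wider uncertainty on the arm-to-arm increments than on the comparisons with control, which the curves will show openly. Follow-up is planned to March 2029, so the change can be made before results are seen.
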